### Assessment of immunity to malaria

Immune responses, antibody and cell-mediated, will be assayed to determine signatures of immunity using plasma and peripheral blood mononuclear cells (PBMCs). For assessment of antibody immunological responses, techniques will include protein microarrays
^44^, antibody-dependent assays of functional immunity such as (GIAs)
^45–
47^, opsonic phagocytosis assays (OPA)
^48^, and antibody dependent respiratory burst (ADRB)
^46,
47,
49^. In further exploratory analysis we will also undertake principal component analyses to determine if there are typical “signatures” of protective responses, and analyses for combinations of protective antigens as previously described by Osier
*et al*. 2014
^17^. The statistical significance of protective antigen combinations will be tested using interaction terms and summary metrics as in previous studies
^17,
50^

A detailed analysis of cellular immune responses in PBMC, plasma and host transcriptomics will be undertaken and include the following: flow cytometry to determine cellular correlates of immunity; determination of the evolution of the T and B cell response at the transcriptomic and cellular levels; RNA sequencing and multiphoton microscopy to study the impact of exposure to parasites on dendritic cells; and determination of the role of antibody-mediated
*P. falciparum* sporozoite inhibition. In addition, the parasite transcriptomes will be analysed as well as assessment of parasite isolates on the day of diagnosis to ensure that the signs and symptoms of malaria observed in the volunteers are not due to community-acquired infections but the infecting parasite strain, NF54.

Table 7 shows a list of proposed exploratory immunological assays to be performed on the samples generated from the study

**Table 7. T7:** List of exploratory immunological assays to be performed on the samples generated from the study
^a^

Assay	Sample type	Reference
Antibody Dependent Respiratory Burst Assay (ADRB)	Plasma	43, 45, 47
Complement Fixation Assay	Plasma	51
DNA microarrays	Parasitised red blood cells (RBCs)	52, 53
Growth Inhibition Assay	Plasma	42, 43, 45
Mass Cytometry (CyTOF) ^1^	PBMCs	53, 54
Merozoite Opsonic Phagocytosis Assay (OPA)	Plasma	46
Multiphoton Microscopy ^2^	PBMCs	55, 56
Metabolomics	Plasma	57
Protein microarrays	Plasma	41
RNA Sequencing ^3^	PBMCs and parasitised RBCs	58
Sporozoite Inhibition Assay	Plasma	59

^a^Other assays will be conducted as and when they are readily available.
^1^Analysis of follicular helper T cells;
^2^Imaging studies of immune-modulatory effects on dendritic cell and T cell interactions; and
^3^T and B cell receptor repertoires including parasite transcriptomics.

***Sample use and storage***. This study will provide a platform for further studies to be conducted using the samples to be collected and stored. Additional ethics approval will be obtained for sub-analyses if different from primary and secondary objectives. The sample set is likely to be an important international resource for testing responses to new candidate antigens for vaccine development, and therefore we will need to store samples to allow further collaborations in the future. These collaborations will be supported if they are consistent with the protocol and as approved by the relevant research ethics committee. Testing outside the permission granted in this protocol will only be supported following an amendment or a new protocol. The samples collected will be stored in the KEMRI-Wellcome Trust Research Programme Kilifi Repository.

### Data management

The principal investigator (PI) will have overall responsibility for ensuring management of the data. A designee to the PI will be responsible for receiving, entering, cleaning, querying, analysing and storing all data that accrues from the study. Responsibility for this may be delegated to the study data management team. The data will be entered into the subjects’ paper
screening CRF and
study CRF
^39^. Data will be subsequently transferred to an electronic database for analysis. If any changes to the study are necessary during the study a formal amendment will be presented to the sponsor prior to submission to the relevant ethical and regulatory agencies for approval unless to eliminate an immediate hazard(s) to study participant without prior ethics approval. Any unforeseen and unavoidable deviations from the protocol will be documented and filed in as a protocol deviation in the Trial Master File, with explanation. A protocol deviation will be any failure to adhere to the defined procedures or treatment plans outlined in the protocol version previously approved by the relevant local research ethics committee. A protocol violation is any planned or inadvertent changes that may impact safety of study participants, affect integrity of the study data and/or affect study participants willingness to participate in the study previously approved by the relevant local research ethics committee. Both deviations and violations will be reported to the relevant local research ethics committee within 10 working days of the deviation/violation. The investigators will formulate a management plan to avoid the occurrence of a similar deviation in future.

***Data capture methods and archiving***. Data capture will be primarily via an offline database for the scheduled visits through use of computers and laptops. These data will then be transferred to an eCRF on Open Clinica. Paper source documents will be used to capture data for the screening visits, unscheduled clinic visits, laboratory and other investigational results. Data on scheduled visits may still be captured on paper source documents if electronic methods are not available. Immunological and PCR data will be transferred to an electronic database for analysis without any volunteer identifier apart from the unique volunteer number. For the social science component, the interviews and discussions will be recorded
^38,
39^. For archiving, the investigator will keep the consent forms and trial master file for at least 5 years after the completion or discontinuation of the trial. The anonymized electronic databases will be maintained beyond this period.

***Data sharing, reporting, and dissemination***. We will make the information on antigen prioritization publicly available and open access as rapidly as possible to provide the widest possible benefit of the study. We will feedback individual results with clinical relevance to volunteers in real-time. Summaries of the outcomes of the trial will be provided during community meetings in the areas from which volunteers are recruited. It is not anticipated that substantial information in this form will be available until at least the third year of recruiting, and this will be made clear during initial meetings to avoid unrealistic expectations regarding the rapidity of feedback.

### Statistics

***Sample size***. Sample size calculations were done considering power of the multivariable model using the powerreg facility from STATA 13, assuming an r
^2^ value of 0.3 for the combined model (i.e. including all variables) indicates 80% power to detect a single variable accounting for 0.15 of the variability in growth rates (after adjusting for other variables) on examining 200 volunteers when 50 variables are included in the model.

***Statistical and analytical plans***. Our analyses of these data will test the following hypotheses: (1) that naturally acquired immunity to malaria depends on responses to specific identifiable antigens; (2) that there are specific thresholds above which immunological responses control parasite growth; and (3) the overall intensity and/or breadth of antibody responses to parasite antigens are associated with immunity. These will be tested using generalized linear models using parasite growth patterns to derive the outcome variable. The parasite growth outcomes will be categorized by analysis of the PCR data and published prior to development of the statistical analysis for immune correlates.

There will be a deliberate analytical framework generated and applied to the data generated. However, this will be largely guided by the outcomes that will be observed and the results for e.g. qPCR. For instance, for parasite growth rates and liver-to-blood inoculums (i.e. the number of parasites exiting the liver and infected red blood cells), these will be calculated by fitting established models to quantitative PCR data. The growth rate will be regressed against the individual immunological measures such as intensity and/or breadth of antibody responses to parasite antigens. Given the co-linearity of responses, a multivariable model is likely to be more informative in testing our hypotheses that: naturally acquired immunity to malaria depends on responses to specific identifiable antigens; and the overall intensity and/or breadth of antibody responses to parasite antigens are associated with immunity. Rather than simply enter all variables in a single multivariable model, we will consider entering variables in clusters and take forward the independent predictors to a final multivariable model. These clusters will be pre-defined and be based on: (a) biological links (for instance grouping all red cell surface antigens separately from merozoite antigens); and (b) on co-linearity (i.e. on clustering groups of antigens with greatest cross-correlations). We will score breadth as the number of antigen responses in the top quartile and mean intensity as the mean of normalized responses for each antigen. These scores will be determined separately for merozoite antigens and for red-cell-surface antigens. We will therefore reduce the dataset to for instance 50 variables, including functional assays, anti-circumsporozoite antibody levels, responses to schizont extract, and scores for mean intensity and breadth which will be added to the final model which will test the hypotheses mentioned above. To test the hypothesis that there are specific thresholds above which immunological responses control parasite growth, we will examine this final model for non-linearity using multiple fractional polynomials and Hill functions to determine if there are discrete thresholds predicting efficacy according to previously used methods.

For the qualitative analysis, the recorded interviews will be transcribed and translated where necessary. The data will be organized and managed using NVIVO 10, a qualitative data management and analysis software. The data will be analysed using a thematic content analysis, which will allow for categorization of the recurrent and common themes and will allow for the presentation of the key elements of the volunteers’ accounts.

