### Enrolment

We will enrol up to a total of 200 volunteers in CHMI. All volunteers will give written informed consent before being enrolled, after having been informed of the nature of the study, the potential risks and their obligations. We will conduct the CHMI studies in groups of 20 to 60 volunteers per cohort as guided by logistic and operational considerations.

***Consent***. All volunteers will sign and date the informed consent form before any study specific procedures are performed. The clinician or investigator will have a checklist for them to discuss with the potential volunteer aimed to assess their understanding of the study. The information sheet will be made available to the volunteer at least 24 hours prior to the screening visit. All informed consent documents will be translated into local languages (Dholuo, Kiswahili and Giriama). Particular points to be covered will be:

Participation in the study is entirely voluntary.Declining to participate involves no penalty or loss of medical benefits.A volunteer may withdraw from the study at any time.A volunteer is free to ask questions at any time to allow him or her to understand the purpose of the study and the procedures involved.There is no direct benefit from participating. The benefits will be realized in the long-term for the community by contributing towards the development of a malaria vaccine.Volunteers will be compensated for travel, time and inconvenience of participating

***Withdrawal criteria***. In accordance with the principles of the current revision of the Declaration of Helsinki (updated 2008) and any other applicable regulations, a volunteer has the right to withdraw from the study at any time and for any reason and is not obliged to give his or her reasons for doing so. The Investigator may withdraw the volunteer at any time in the interests of the volunteer’s health and well-being. In addition, the volunteer may withdraw/be withdrawn for any of the following reasons:

Administrative decision by the InvestigatorIneligibility (either arising during the study or retrospectively, having been overlooked at screening)Significant protocol deviationVolunteer non-compliance with study requirements

***Managing withdrawals***. The reason for withdrawal will be recorded in the
study case report form (CRF)

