***Publication policy***. Results will be published in an open-access journal. Anonymized data on PCR values and immunological data will be made available with these publications. The scientific and intellectual contributions of all persons involved in the research will be appropriately acknowledged in all publications and presentations arising from the work.

***Study status***. Ethical approval for CHMI-SIKA was granted in March 2016 and the study started enrolment in August 2016. To date (30th October 2019) we have enrolled 161 volunteers with two DSMC meetings. The foregoing protocol is written in the future tense reflecting that work is ongoing.

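### The stated 80% power does not follow from its own inputs: 200 volunteers, 50 variables, full R² 0.3 and one variable worth 0.15 give over 99.9% power at 5%

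*Protocol article*

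**What the plan says.** The sample-size paragraph of the protocol article (Statistics) reports a multiple-regression power calculation made "using the powerreg facility from STATA 13". Its inputs are:

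- a total R² "value of 0.3 for the combined model (i.e. including all variables");
- an effect described as "a single variable accounting for 0.15 of the variability in growth rates (after adjusting for other variables");
- a sample given as "on examining 200 volunteers";
- 50 variables in the model.

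The claimed result is that this "indicates 80% power to detect a single variable accounting for 0.15 of the variability in growth rates". The sentence gives no significance level, number of variables tested or allowance for losses.

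Three other places bear on the sample size:

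- Enrolment makes 200 a ceiling: "We will enrol up to a total of 200 volunteers in CHMI".
- Managing withdrawals, in the same section, removes volunteers withdrawn before they meet the malaria criterion from the primary analysis.
- Study status, under Ethical compliance, reports: "To date (30th October 2019) we have enrolled 161 volunteers".

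**The concern.** A variable that alone explains 15% of the outcome variance, net of everything else in the model, is a large effect for 200 people. Fifty predictors still leave 149 residual degrees of freedom, so power as low as 80% is implausible on its face.

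This sentence is the only rationale in the article for deliberately infecting up to 200 volunteers. The primary objective is to relate antibody levels to parasite growth so that antigens can be prioritised. A reader who trusts the sentence will think an antigen must explain about 15% of growth-rate variance to be found reliably, and will read a null result as ruling out only effects of that size. The sentence also hides how much room there is for multiplicity control across some 50 variables at the planned effect.

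**Working it through.** **Inputs (Statistics, sample-size paragraph).** N = 200; predictors k = 50; full-model R² = 0.30; unique increment of the tested variable = 0.15, so the model without it has R² = 0.15; one variable tested. Alpha is not stated. I take two-sided 0.05 and also 0.05/50 = 0.001.

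**Formula.** F test for an R² increment:

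- f² = (R²full − R²reduced)/(1 − R²full) = (0.30 − 0.15)/(1 − 0.30) = 0.2143
- df1 = 1; df2 = N − k − 1 = 200 − 50 − 1 = 149
- power = P(F′(df1, df2, λ) > Fcrit), with Fcrit = 3.90 at alpha 0.05 and 11.27 at 0.001

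Three conventions for the non-centrality λ are in use, so all are shown.

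**Attempt to reproduce 80%.**

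| Convention | λ | Power, alpha 0.05 | Power, alpha 0.001 |
|---|---|---|---|
| N·f² | 200 × 0.2143 = 42.9 | 99.9997% | 99.91% |
| (df1 + df2 + 1)·f² | 151 × 0.2143 = 32.4 | 99.989% | 98.9% |
| df2·f² | 149 × 0.2143 = 31.9 | 99.987% | 98.8% |

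The stated figure is not reproduced. To bring power down to 80%, alpha would have to be about 7 × 10⁻⁸ (first convention) to about 4 × 10⁻⁶ (third).

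**Other readings of the sentence.**

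- 0.15 as a partial R² (f² = 0.15/0.85): 99.91% to 99.996% at 0.05, and 95.9% to 99.4% at 0.001.
- 0.15 as the joint contribution of 49 or 50 variables, alpha 0.05: about 88% under the first two conventions, about 72% under the third.
- A 50-variable model with total R² 0.15, tested against nothing: 77% under the first two conventions, 60% under the third.
- 0.15 as a correlation (increment 0.0225), λ = N·f²: 71% at two-sided 0.05, 81% at one-sided 0.05.
- 0.15 before adjustment, with 81% of the variable's own variance explained by the other predictors, λ = N·f²: 81%.

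The readings that come near 80% conflict with the text, which specifies a single variable, a share of variability, and adjustment for the others.

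**What the inputs do support.** Holding k = 50, full R² = 0.30 and 80% power, I solved for the unique R². Ranges run across the first two conventions; the third moves the upper ends only slightly, for example to 0.083 at N = 200 and alpha 0.001.

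| N | Detectable unique R², alpha 0.05 | Detectable unique R², alpha 0.001 |
|---|---|---|
| 200 | 0.028–0.037 | 0.062–0.082 |
| 161 | 0.035–0.050 | 0.078–0.112 |

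At N = 200 and alpha 0.05, 0.15/0.037 = 4.1 and 0.15/0.028 = 5.4, so the detectable effect is some four to five times smaller than stated. At 0.001, 0.15/0.082 = 1.8 and 0.15/0.062 = 2.4, so it is about half the stated effect.

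The smallest N giving 80% power for an increment of 0.15 is 57, 88 or 90 at alpha 0.05, depending on convention, and 92 to 137 at 0.001.

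**The case against.** The best reply accepts the arithmetic and questions what is built on it.

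1. **The faulty input is unknown.** The mismatch shows only that at least one reported item is wrong. The effect size is the natural suspect, but the number of variables tested, the R² or the power could be the misreported one. A joint test of 49 or 50 variables spans about 72% to 88% across conventions, which brackets 80%, and the paragraph opens by speaking of the power of the multivariable model. This stands as a caution about the cause. It does not rescue the sentence, and the detectable effects above are correct for the stated N, number of variables and R² whichever input slipped.

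2. **The error is conservative.** At the stated effect the trial has more power than claimed, and nobody's participation changes. True, but the figure is still wrong, and it is the one readers will use to interpret null results.

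3. **The recomputed effects describe one fixed 50-variable linear model.** The analysis plan selects variables in clusters, speaks of categorising growth outcomes, and gives 50 only as an example. Real power may be lower. This stands: the corrected figures are what the stated inputs give, not a guarantee for the final analysis.

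4. **Losses are a side issue.** Correct for the stated effect: even 100 volunteers give 89% to 99.5% power at 0.05. Losses matter only for the smaller effects that a corrected sentence would quote, and 161 is an interim count, not an analysis set.

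5. **A condensed article may leave alpha and similar details to the full protocol or analysis plan.** Agreed, and their absence is not the complaint. The complaint is that the printed figures contradict each other at any plausible alpha.

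**Conclusion.** The concern holds. On the stated inputs, power for a single variable with unique R² 0.15 is at least 99.98% at two-sided 0.05 and at least 98.8% at 0.05/50, against 80% stated. With 200 volunteers, 80% power corresponds to a unique R² of about 0.03 to 0.04 at 0.05, or about 0.06 to 0.08 at 0.05/50.

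This rests on the standard F test for an R² increment, on reading 0.15 as the share left after adjustment (as the text says), and on an assumed alpha, since none is given. The choice among the three non-centrality conventions does not alter the conclusion. Which input was misreported cannot be settled from the article. The trial is not underpowered for the effect it names; what is missing is a valid basis for 200 and a correct statement of what 200 can detect.

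**What to change.** Retrieve the original calculation, rerun it, and replace the sentence. For the stated N, number of variables and R², the wording would be along these lines: with 200 volunteers, 50 variables and a full-model R² of 0.3, there is 80% power for a single variable with a unique R² of about 0.03 to 0.04 at two-sided 0.05, or about 0.06 to 0.08 at 0.05/50. If the rerun shows that a different quantity was tested, such as a block of variables, describe that instead.

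In either case, name the alpha, the number of variables tested and the non-centrality convention, which reduces each range to one value. Give the same figure for the number of volunteers expected to have an analysable growth rate, since 200 is a maximum and some withdrawals leave the primary analysis.

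The cost is one sentence in the protocol or analysis plan, best settled before the immune-correlate analysis. Enrolment does not change.

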## Abstract

Malaria remains a major public health burden despite approval for implementation of a partially effective pre-erythrocytic malaria vaccine. There is an urgent need to accelerate development of a more effective multi-stage vaccine. Adults in malaria endemic areas may have substantial immunity provided by responses to the blood stages of malaria parasites, but field trials conducted on several blood-stage vaccines have not shown high levels of efficacy.  We will use the controlled human malaria infection (CHMI) models with malaria-exposed volunteers to identify correlations between immune responses and parasite growth rates
*in vivo*.  Immune responses more strongly associated with control of parasite growth should be prioritized to accelerate malaria vaccine development. We aim to recruit up to 200 healthy adult volunteers from areas of differing malaria transmission in Kenya, and after confirming their health status through clinical examination and routine haematology and biochemistry, we will comprehensively characterize immunity to malaria using >100 blood-stage antigens. We will administer 3,200 aseptic, purified, cryopreserved
*Plasmodium falciparum* sporozoites (PfSPZ Challenge) by direct venous inoculation. Serial quantitative polymerase chain reaction to measure parasite growth rate
*in vivo* will be undertaken. Clinical and laboratory monitoring will be undertaken to ensure volunteer safety. In addition, we will also explore the perceptions and experiences of volunteers and other stakeholders in participating in a malaria volunteer infection study. Serum, plasma, peripheral blood mononuclear cells and whole blood will be stored to allow a comprehensive assessment of adaptive and innate host immunity. We will use CHMI in semi-immune adult volunteers to relate parasite growth outcomes with antibody responses and other markers of host immunity.

**Registration:** ClinicalTrials.gov identifier
NCT02739763.

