## Discussion

Malaria transmission is an ongoing public health problem in Africa. There is an urgent need to accelerate the development of a more effective vaccine. Accelerating the development of a malaria vaccine will be of substantial benefit. The controlled human malaria infection model in semi-immune adults helps overcome a critical block in vaccine development, i.e. comprehensive prioritization of antigens associated with blood-stage immunity for vaccine development. This will be the largest CHMI study in malaria-exposed individuals and will provide data relating to how naturally acquired immunity to malaria depends on specific responses and that overall intensity and/or breadth of antibody responses are associated with immunity. The outcome will determine antigen selection for the next generation of blood-stage malaria vaccines. In our experience of conducting these studies, we found it beneficial to embed social science framework studies to understand perceptions of such type of studies in endemic populations. We implemented this in the second cohort of recruitment and was considered in the first CHMI study conducted in Kenya
^35^. We drew on recommendations from Njue
*et al*.
^38^ to shape and change some of the practices of conducting the study. Thus, this study will not only contribute new knowledge on potential correlates of protection in the context of naturally immunity, but the sample set generated will also allow for additional sub-studies to be performed to further unravel our understanding of immunity to malaria. Furthermore, this will also contribute to our understanding on how to undertake these types of studies through embedded social science sub-studies. This study also aims to build a stronger and more grounded understanding of the ethics of research using the CHMI model to inform future research in this context, and potentially in other similar settings.

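### Predictors of growth chosen within clusters are tested again in a final model on the same volunteers, with no stated validation or error control covering the selection

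*Protocol article*

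**What the plan says.** The Abstract gives the scale of the search: "we will comprehensively characterize immunity to malaria using >100 blood-stage antigens", in up to 200 volunteers. The primary objective is the correlation between antibody levels and parasite growth rate. Hypothesis 1, in the Statistics section, is that immunity depends on responses to particular antigens that can be identified.

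The same section describes the route to that test:

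- **Clusters.** "These clusters will be pre-defined and be based on: (a) biological links", and also on co-linearity.
- **Selection.** "we will consider entering variables in clusters and take forward the independent predictors to a final multivariable model".
- **Reduction.** "We will therefore reduce the dataset to for instance 50 variables". These include functional assays, anti-circumsporozoite antibody, schizont-extract responses, and intensity and breadth scores.
- **Testing.** The reduced set is "added to the final model which will test the hypotheses mentioned above". The final model is then examined for thresholds with fractional polynomials and Hill functions.

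The sample size statement claims 80% power for one variable with a 0.15 share of growth-rate variability, given an R² "value of 0.3 for the combined model (i.e. including all variables"), "on examining 200 volunteers when 50 variables are included in the model". It states no significance level. The article also says that the immune-correlates analysis will be developed after the growth outcomes have been published.

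**The concern.** Whether a variable is an independent predictor of growth can be judged only by looking at growth. The selection step therefore uses the outcome, and the survivors are tested against that same outcome in the same people. Their p-values, coefficients and the model R² then take no account of the search that put them there. Fixing the clusters in advance does not cure this, because the choice within each cluster still depends on the outcome.

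This is the analysis of the primary objective. The article labels its principal component and antigen-combination analyses exploratory, but not this one. The Discussion says "The outcome will determine antigen selection for the next generation of blood-stage malaria vaccines", so an antigen named in error could enter vaccine priorities.

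**Working it through.** **1. The plan's own power figure.** Inputs from the Statistics section: N = 200, 50 variables, full-model R² 0.30, unique share 0.15.

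- f² = 0.15 / (1 − 0.30) = 0.214; F test with 1 and 200 − 50 − 1 = 149 degrees of freedom.
- Noncentrality: f² × 200 = 42.9, or f² × 149 = 31.9 under the alternative convention.
- Power at an assumed two-sided 0.05: above 99.9%. At 0.05/50: 98.8–99.9%. At 0.05/100: 98.0–99.8%.

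The stated 80% does not reproduce. That is a separate point. What matters here is that the 80% does not conceal an adjustment for 50 or 100 tests.

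**2. Simple bounds with independent null variables at 5%.**

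- 100 tests: 1 − 0.95^100 = 99.4%, with 100 × 0.05 = 5 false positives expected.
- 50 tests in the final model alone: 1 − 0.95^50 = 92.3%.

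**3. Simulation of the two steps.** Setting: N = 200, 100 antigens unrelated to a continuous growth rate, 2 to 20 clusters, correlations from 0 to 0.9. Least squares is run within each cluster, variables with p below the threshold are kept, the survivors are refitted on the same 200, and those again below the threshold are counted. The number of clusters, the correlations, the threshold and the p-value rule are assumptions; the article gives none of them.

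| Assumed level at both steps | Null antigens passing selection (mean) | False predictors in final model (mean) | Chance of at least one | Selected null antigen confirmed |
|---|---|---|---|---|
| 10% | about 10 | 5.6–6.6 | 98–99.9% | 56–65% |
| 5% | about 5 | 2.0–3.4 | 75–98% | 41–68% |
| 1% | about 1 | 0.2–0.7 | 13–49% | 22–69% |

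The 10% and 1% rows use 10 clusters. If selection were harmless, the last column would equal the level in the first. At 5%, uncorrelated antigens give 95–98%, and antigens correlated both within and across clusters give 75–89%. Adding 45 further null variables to the final model, to approach the planned 50, gives 83%.

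**4. Whether a later correction repairs it (5% screen).**

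- Bonferroni over the survivors only: 60–75% chance of a false predictor.
- 0.05/100 applied in the final model after same-data selection: about 5–18% with 10 or 20 clusters.
- Selection in 100 volunteers, testing in the other 100: 20–22% unadjusted, 4–6% with Bonferroni over survivors.
- One model with all 100 antigens and Bonferroni, no pre-selection: 5–6%.

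**5. Cost in power of strict control** (50-variable model, N = 200, R² 0.30).

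| Unique R² | Power at 0.05 | Power at 0.0005 |
|---|---|---|
| 0.15 | >99.9% | 98–99.8% |
| 0.05 | 90–96% | 39–59% |
| 0.03 | 71–83% | 16–27% |

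**The case against.** The strongest defence is that this is a condensed article. It promises an analytical framework and defers the correlates analysis, and error control is commonly left to a statistical analysis plan. That is right as far as it goes: silence on multiplicity is no finding, and a reader should not infer that none will be applied. What remains is the sequence that the article does state, with the hypotheses tested in a model filled by selection on the same volunteers. A routine adjustment added later to the final model would not mend it (item 4 of the working).

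Three stronger readings are tempting and not supported:

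- **That antigens are screened by significance.** The article gives no criterion, and the cluster step is something the authors will only consider. A p-value rule is a natural reading, not a stated one.
- **That false predictors are near certain.** This holds for weakly correlated antigens at 5% or for a looser screen. With correlated antigens at 1% it is well under 50%.
- **That strict control costs almost nothing.** This holds only for the very large effect in the sample size statement, half of the assumed total R². With more than 100 correlated antigens sharing an R² of 0.3, smaller effects are plausible, and for those Bonferroni is expensive.

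It is also fair to say that clusters built on biology or cross-correlation, and breadth and intensity scores, are described without reference to the outcome. That part of the data reduction creates no double use.

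**Conclusion.** The concern holds for the procedure as written: outcome-based selection followed by hypothesis tests on the same volunteers, with nothing stated that separates the two or carries the selection into the inference. Final-model p-values and R² would not be valid evidence for hypothesis 1. If 5% per test is used at both steps and no antigen matters, two to three false predictors are expected, with a 75–98% chance of at least one. At 1% the chance is 13–49%.

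These figures assume 100 antigens all unrelated to growth, a continuous growth rate and a simple p-value screen. They leave out the threshold search, which is a further search on the same data. They measure the hazard of the stated sequence; they do not predict this study's result. The deferred correlates plan can still resolve the point if it settles the matter before the antibody data are related to growth.

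**What to change.** Amend the Statistics section, or fix in the correlates plan before that analysis is run:

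1. Ordinary p-values and R² from the final model will be descriptive and will not serve as tests of hypothesis 1.
2. A global test will permute growth outcomes among volunteers within challenge cohort and rerun the whole pipeline, selection included. This tests only whether any antigen is related to growth; it does not by itself give valid p-values for single antigens when others truly matter.
3. Claims about single antigens will come from a single-step analysis of all antigens measured, or from a sample split, with multiplicity or FDR control over every antigen tested. The article already plans to regress growth on individual measures, which could serve as the single-step analysis for marginal associations.
4. R² will come from cross-validation that repeats the selection in every fold.
5. The selection criterion and the significance or FDR level will be written down.

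The cost is wording and code, with no new volunteers, samples or assays. Fewer antigens will be nominally significant. Sample splitting also halves the data for each step: for the protocol's effect, power in the testing half is about 83–98% with 5 to 20 survivors, provided that the variable was selected. Because Bonferroni at 0.05/100 would cut power to 39–59% for a unique R² of 0.05, FDR control is the more reasonable choice for a study meant to rank antigens.
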